## Abstract

**Background:**

Despite major gains in smoking cessation treatment, over half of those who recently quit will relapse within one year. Two systematic reviews of relapse prevention studies reached differing conclusions on the effectiveness of behavioral interventions. Existing relapse prevention evidence is limited by study designs, methodology, and conceptual approaches to behavioral interventions. Personal networks exert powerful effects on initiating and maintaining smoking behavior and can facilitate maintaining abstinence or trigger relapse. To date, relapse prevention interventions have focused on those who are newly abstinent (“abstainers”) and have not attempted to influence the abstainer’s personal network. The Helpers Stay Quit (Helpers Stay Quit) online training is a conceptually novel “help others” intervention to increase abstainers’ public identification as a nonsmoker and their ability to influence those in their personal network to also quit smoking—thereby creating a personal network social environment supportive of long-term abstinence.

**Objective:**

This study is a 2-arm, pragmatic randomized controlled trial (pRCT) testing the hypothesis that quitline abstainers receiving the Helpers Stay Quit intervention will have higher 30-day and 7-day point prevalence of abstinence than those receiving quitline follow-up usual care, and that outcomes may be mediated by characteristics of abstainers’ personal networks. The embedded mixed methods study examines the effects of the Helpers Stay Quit intervention on the abstainers’ personal network interactions related to smoking and smoking cessation.

**Methods:**

The study design is a 2-group pRCT (N=940) comparing the Helpers Stay Quit online training intervention with a quitline usual care condition. Baseline, 3-, 6-, and 12-month surveys collect data on cognitive and emotional factors potentially influencing relapse. Text messages survey tobacco use status and participants’ use of the Helpers Stay Quit training content. The composition and structure of participants’ personal networks are assessed at baseline and 12 months. We interviewed 60 participants (both relapsed and abstinent) at differing intervals in the last 6 months of study participation to qualitatively assess personal network influences on relapse or abstinence.

**Results:**

A total of 9 state quitlines are participating by referring potentially eligible clients for screening and potential enrollment. Recruitment began in December 2022. Enrollment of 940 participants was completed in September 2025. When the manuscript was submitted, as of August 31, 2025, 337 participants (65%) had completed the study with 12-month follow-up surveys.

**Conclusions:**

This pRCT tests whether exposure to the Helpers Stay Quit intervention decreases relapse rates of newly abstinent smokers enrolled in state quitline coaching treatment. The embedded personal network mixed methods study is designed to examine the characteristics of a newly abstinent smoker’s personal network that may influence relapse and the potential spread of cessation-related information and behaviors through their personal network. The study’s design and measures will provide insights into the influences of personal networks and the cognitive and emotional factors impacting the likelihood of relapse or maintaining abstinence in those who are newly abstinent.

## Introduction

### Background

Effective tobacco dependence treatments are more numerous and accessible than ever before [1,2]. However, tobacco use remains the leading preventable cause of premature morbidity and mortality in the United States. In addition, cessation treatments are severely underused [3-5], due to both knowledge and attitudinal barriers (eg, low awareness of and misinformation about cessation medications’ effectiveness, safety and proper use, and negative attitudes about seeking counseling or other behavioral support for quitting) [6-9]. Despite major gains in the use of smoking cessation treatment, over half of those who have recently quit will relapse within the first year. In an analysis of prospective data from a large representative sample of the general population of the United States, the risk of relapse is more than 50% [10] for abstainers with less than 12 months of abstinence. Identifying effective relapse prevention strategies will enable more individuals to maintain their abstinence beyond a year and, consequently, prevent tobacco-related morbidity and mortality.

Published research on smoking relapse prevention has limitations in methodological design and intervention approaches. Two systematic reviews of relapse prevention interventions reached differing conclusions regarding the efficacy of behavioral interventions [11,12]. Agboola et al [11] concluded minimal self-help intervention was effective. Livingstone-Banks et al [13] concluded with only “moderate certainty” that behavioral interventions were not effective, with the caveat that “further research is likely to have an important impact on our confidence,” [13] and a recommendation that future relapse prevention research examine alternative behavioral approaches [13]. A critique of extant research cited methodological weaknesses and limited conceptual approaches to treatment [13]. Different approaches to both studies of relapse prevention and to the interventions themselves are needed to advance the long-term understanding and outcomes of smoking relapse prevention. Livingstone-Banks et al recommended randomization of smokers who were already abstinent (“abstainers”) as the strongest design for relapse prevention studies [13]. The protocol for a pragmatic randomized control trial (pRCT) we present here addresses both methodological and treatment approach limitations of extant research.

### Conceptual Basis for the Helpers Stay Quit Intervention

Conceptualizing relapse as a dynamic process is the organizing framework [14] guiding the overall Helpers Stay Quit intervention and our evaluation approach. Within this working model, relapse susceptibility or “Relapse Proneness” [15] shifts as a function of physiological, environmental, and cognitive components, each independently contributing to relapse risk at various points in the continuum from quit attempt to long-term abstinence. Relapse proneness results from the interplay of 3 forces—2 of which are cornerstones of relapse research: physical withdrawal symptoms and triggers. The third, more speculative force—“cessation fatigue”—is a latent construct operationalized by declines in motivation, expectancy for success, coping attempts, self-efficacy, and self-control resources [14]. It has been suggested that exploration of “cessation fatigue” may illuminate new possible mechanisms related to relapse [15-17]. To address the dynamic and complex nature of the relapse process and to guide the approach for the proposed pRCT, the conceptual model for the intervention and study uses an integration of interpersonal [18,19], social network [20], social support [21], behavioral theories and concepts and stress and coping theories [22], and Helper Therapy Principle [23] to examine the interrelatedness, time sensitivity, and potential feedback loops related to relapse outcomes [16]. Helpers Stay Quit is novel in its integration of the above theories into an intervention model that is presented as helping others and teaches trainees how to offer a “helping conversation” to help others quit.

### Personal Networks and Smoking Behavior

Personal networks exert powerful influences on smoking and quitting behavior [24]. Efforts to increase the use of cessation aids have focused almost exclusively on the smoker [25,26]. Personal networks, wherein abstainers (“egos”) are in direct contact with members of their personal network (“alters”), warrant exploration as an avenue for relapse intervention. Personal networks can provide positive feedback and support for abstinence. Importantly, personal networks can also be sources of powerful cues to smoke and ready access to cigarettes—directly impacting relapse risk [27-31]. Personal networks may be an important part of the relapse process, but little is known about how relationships and exchanges of knowledge and information between people in the network feed back into the cessation context. Cessation behavior transmission can occur within three degrees of separation from the original quitter [32], suggesting network-based interventions may be beneficial for initiating quit attempts beyond the abstainer’s personal network. In previous work, 89% of general community member participants (n=906) were motivated to enroll in our study to learn tobacco cessation skills to help a friend or family member quit [33]. Furthermore, the majority of participants (up to 80%‐86%) [34,35] reported taking action to help others quit, including offering information and referrals [35,36] primarily to persons in their personal network [35,36].

### Preliminary Evidence Supporting Helpers Stay Quit for Relapse Prevention

We conducted a single-group, observational, pilot feasibility study of Helpers Stay Quit, with an embedded personal network study (n=104), to assess design, methods, and procedures in preparation for the current pRCT and personal network study protocol presented in this paper. Participants were cigarette smokers enrolled in Arizona’s state quitline coaching service contacted for routine follow-up approximately 14‐30 days after their quit date and reporting abstinence from smoking (not even a puff) for at least 14 days. Eligible participants were adults, able to speak and read English, had access to a computer to take the online Helpers Stay Quit training, had a mobile phone to receive and send text messages, agreed to participate in two personal network interviews, and consented to share their quitline client data with the research team. Participants completed online questionnaires at baseline, 3 months, and 6 months, querying smoking status and other behavioral measures related to smoking and cessation. Monthly text message surveys queried smoking status and offering of helping conversations. Personal network telephone interviews were conducted at baseline and 6 months.

We used propensity score matching to compare the quitline clientele with the feasibility study sample at 6‐7 months. Matches were drawn from deidentified data from the quitline’s complete participant pool for the 2-year period corresponding to the study in a ratio of 4 to 1. Variables for matching included age (>50 years vs 18‐50 years), sex (male vs female—no nonbinary participants were enrolled), race and ethnicity (non-Hispanic White, Hispanic, and non-White non-Hispanic), Fagerström score (>5 vs 1‐6), and presence of a chronic condition (any vs none). Study results showed Helpers Stay Quit participants reporting higher 30-day abstinence than nonparticipants (86% vs 36%; difference 49%, 95% CI 40%-59%; *P*<.001) [37].

Participants in the longitudinal embedded personal network study (egos) completed a personal network telephone interview in which they named members of their personal network with whom they had at least monthly contact (alters). With each monthly text message survey, egos who reported offering a helping conversation were given a link to an online survey that could be passed to an alter who could respond anonymously. The alter survey queried smoking status, content of the helping conversation, and the alter’s reaction to the helping conversation. Results showed that a participant’s behavior to help others quit extended to their personal networks, where 89% of abstainers offered helping conversations, and 86% abstained from smoking for the 6-month study duration (n=64) [38]. Abstaining individuals significantly increased the number of nonfamily members (mean difference [MD] 1.41; *P*<.001) and smokers in their networks (MD 0.77; *P*=.006) at follow-up. This change provided participants with more opportunities to carry out helping conversations. After receiving a helping conversation, alters reported positive changes in cessation-related behavior. These findings further support the potential of personal network behavioral interventions, like Helpers Stay Quit, to facilitate smoking relapse prevention.

### Research Objectives

This study is designed to assess the effect of Helpers Stay Quit training on the proportion and duration of participants maintaining abstinence or relapsing over time and on participants’ personal network structure and interactions related to smoking and smoking cessation. Primary and secondary research questions are as described in study-specific aims (Textbox 1).

Textbox 1.The Helpers Stay Quit study-specific aims.Aim 1: Using a 2-group, pragmatic randomized, controlled trial (pRCT; N=940) in which abstinent smokers (2-6 weeks abstinent) are randomized to the Helpers Stay Quit intervention or quitline follow-up usual care, to evaluate the effectiveness of Helpers Stay Quit on:Smoking status (30-day and 7-day point prevalence abstinence) at 6- and 12-month intervals (primary outcome).The number, timing, and duration of participants’ lapses and relapses to smoking (secondary outcome).Rates of participants’ self-reported delivery of helping conversations to other tobacco users (secondary outcome).Aim 2: embed a mixed methods social network study into the pRCT to examine the Helpers Stay Quit effects on:Composition and structure of participants’ personal networks.Characteristics of participants’ personal networks over the course of the study (eg, proportion of smokers in personal network).Spread of smoking cessation-related information, assistance, and behaviors from participants to others in their personal networks.Recipients of helping conversations report about smoking-related interactions and information exchange with participants and associated cessation-related behavior change.Aim 3: using personal network metrics derived from the personal network study (eg, size, composition, and structure), conduct mediational analyses of personal network effects on the primary and secondary study outcomes in Aim 1.

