## Methods

### Study Design

This is a 2-group, parallel pRCT with embedded personal network study comparing: (1) Intervention: Helpers Stay Quit training, and (2) control: quitline postabstinence follow-up usual care. The primary outcome is smoking status at 6 and 12 months. The purpose of the pRCT is to assess if a novel behavioral intervention (Helpers Stay Quit) overall has any effect on relapse in newly abstinent smokers following standard quitline treatment compared to quitline usual care, in real-world conditions of serving state quitline client populations. Relapse and the number of helping conversations will be assessed using a text survey weekly for the first 6 months and biweekly for months 7‐12. The prestudy quitline treatment, quitline referral, study recruitment, screening, consent, and prerandomization and run-in period are depicted in Figure 1. The postrandomization study intervention exposure, assessment intervals, and qualitative interviews are depicted in Figure 2.

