#### Relapse Status (Primary Outcome) and Helping Conversations (Secondary Outcome)

Smoking or other tobacco use, electronic nicotine delivery device use, use of cessation aids, and helping conversations are assessed by online surveys at baseline, 3, 6, and 12 months, and by weekly text message surveys for months 1‐6, then biweekly text surveys for months 7‐12. Relapse is defined as (1) any smoking on 7 consecutive days or (2) smoking at least once each week over 2 consecutive weeks. Multiple relapses are defined as relapsing, reporting being quit (7-day point prevalence), and then subsequently reporting smoking again. Offers of helping conversations are assessed by baseline survey and weekly text message surveys (months 1‐6), then biweekly text surveys (months 7‐12). A 5-point Likert scale queries confidence in helping conversations, for example, talking to others about quitting smoking. Content of typical helping conversation (eg, setting quit date, quit plan, cessation medication, quitline referrals, and avoiding relapse) is queried via a yes or no checklist at baseline, 3, 6, 9, and 12 months (Table 1).

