### Sample Size, Power Estimates, and Analysis

#### Power and Sample Size for Pragmatic Randomized Controlled Trial (pRCT)

A sample size of 940 participants would yield 80% power to detect a difference in smoking cessation rates between arms of 10%, assuming a conservative control arm rate of 0.25 [65], 30% dropout, and a noncontinuity corrected *χ*^2^ test. This difference is smaller than that found in the preceding pilot feasibility study (difference=46%); this effect size was chosen as a clinically significant difference with public health implications and is feasible, given the pilot results. This sample size also yields 90% power to detect standardized effect sizes for continuous secondary outcomes of Cohen *d*=0.26, a small-to-medium effect size, and considered to be a good estimate for a minimum important difference for patient-reported outcomes.

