##### Aim 1: Abstinence and Relapse

Abstinence rates at 6- and 12-months postrandomization and biochemically confirmed abstinence at 6- and 12-months postrandomization will be compared between arms using multivariable logistic regression for each outcome (6- or 12-months). Independent variables will include intervention status, strata (race and ethnicity), quitline, and covariates (as described above). We will compare time to first relapse using Cox models and Kaplan-Meier curves. The number of relapses and helping conversations will be compared between study arms using Poisson regression, with the zero-inflated Poisson or negative binomial model used if appropriate. We will carry out secondary analyses using general linear mixed models to examine change in cognitive and emotional measures of participant-reported outcomes (described above in the General Quantitative Approaches section) for participants randomized to receive Helpers Stay Quit compared to participants randomized to the usual care arm.

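### Four abstinence endpoints share the primary label with no deciding one, while the 80% power fits a single comparison whose window and time point are not named

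*Protocol article*

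**What the plan says.** - **Research Objectives, Textbox 1, Aim 1** sets the primary outcome: "Smoking status (30-day and 7-day point prevalence abstinence) at 6- and 12-month intervals (primary outcome"). Two windows at two times make four endpoints under one label.
- **Study Design** restates it without a window: "The primary outcome is smoking status at 6 and 12 months".
- **Abstract, Objective** gives the hypothesis that the intervention arm "will have higher 30-day and 7-day point prevalence of abstinence than those receiving quitline follow-up usual care". It names no time point.
- **Aim 1: Abstinence and Relapse** says that abstinence rates "will be compared between arms using multivariable logistic regression for each outcome (6- or 12-months"). The same sentence also lists biochemically confirmed abstinence at both times.
- **Power and Sample Size for the pRCT** states: "A sample size of 940 participants would yield 80% power to detect a difference in smoking cessation rates between arms of 10" percent, "assuming a conservative control arm rate of 0.25 [65], 30% dropout, and a noncontinuity corrected" chi-square test. It names no window, time point, alpha or sidedness.
- **Measures section heading** reads "Relapse Status (Primary Outcome) and Helping Conversations (Secondary Outcome"), although Textbox 1 lists the number, timing and duration of lapses and relapses as secondary.

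**The concern.** A trial with one powered comparison and four endpoints called primary has no stated way of turning four results into one conclusion. The four can disagree: an effect may appear at 6 months and fade by 12, or hold for one window and not the other. Whoever reads the results could then call the trial positive or negative according to which endpoint is put first. The stated operating characteristics depend on that choice. Counting any significant endpoint as success raises the false-positive rate. Requiring all of them lowers the power. The single figure of 80% applies to neither rule.

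The article's closing section says that results will be reported according to the plans it describes, so readers will hold the trial to this text.

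**Working it through.** **Inputs from the protocol article.** Control rate 0.25, difference 0.10 (so 0.35 in the intervention arm), 80% power, 30% dropout, chi-square test without continuity correction, N=940 in two arms of 470.

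**Step 1: reproduce N.** With p̄ = 0.30 and a two-sided alpha of 0.05:

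n = [1.96·√(2·0.30·0.70) + 0.8416·√(0.25·0.75 + 0.35·0.65)]² / 0.10²
= [1.2702 + 0.5422]² / 0.01 = 328.5, so 329 per arm.

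2·329 / 0.70 = 940. Power at 329 per arm is Φ[(0.10·√329 − 1.2702)/0.6442] = Φ(0.844) = 80.1%.

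Variants that miss 940:

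| Variant | Total N |
|---|---|
| Two-sided 0.05, continuity corrected | 998 |
| One-sided 0.05, uncorrected | 740 |
| One-sided 0.05, corrected | 798 |
| Two-sided 0.025 (split over two) | 1138 |
| Two-sided 0.0125 (split over four) | 1336 |

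So 940 fits one test at an undivided two-sided 5%, with no allowance for several primary endpoints.

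**Step 2: four tests, each at 5%.** If the four were independent, the chance of at least one false positive would be 1 − 0.95⁴ = 18.5%. They are strongly correlated, so this is only an upper reference. The documents give no correlation and no 7-day rate, so both are assumed:

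- 329 per arm.
- Control rates of 25% (30-day) and 30% (7-day, assumed). 30-day abstinence is nested within 7-day abstinence.
- Latent correlation between 6 and 12 months of 0.6 to 0.9 (assumed).
- Under the alternative, a 10-point effect on every endpoint.

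Simulated results, 20,000 replicates per setting:

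| Latent correlation | Any of four, null | Any of two times (30-day), null | Any of four, power | All four, power | Both times (30-day), power |
|---|---|---|---|---|---|
| 0.60 | 13.2% | 9.4% | 94.6% | 58.6% | 67.9% |
| 0.75 | 12.6% | 8.8% | 93.3% | 60.1% | 69.0% |
| 0.90 | 11.6% | 8.3% | 91.4% | 62.8% | 71.8% |

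Allowing for differences between runs, all-four power is about 58–64%. A second approach sets correlations directly on the test statistics (0.7 to 0.95 between windows, 0.5 to 0.8 between times) and uses 25% against 35% throughout. It gives about 10–15% for any false positive, 90–96% power for any, and 57–69% for all four.

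**Step 3: splitting alpha at the existing size.** Power per test for 25% against 35% at 329 per arm:

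- Alpha 0.025 (two endpoints): Φ[(1.8138 − 2.2414·0.6481)/0.6442] = Φ(0.561) = 71%.
- Alpha 0.0125 (four endpoints): Φ[(1.8138 − 2.4977·0.6481)/0.6442] = Φ(0.303) = 62%.

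**The case against.** **The SAP is not shown and this is a condensed article.** A multiplicity method or hierarchy may sit in the SAP, and its absence here is no finding. That stands. What remains is in the text itself: one primary label covers four endpoints, and the power statement does not say which of them it describes.

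**A reader might infer that each endpoint is tested at full alpha, so that both the 5% error rate and the 80% power fail.** The article does not support this. It states no alpha for the primary comparison. The 5% is back-calculated from N and shows only how the trial was sized. The two harms are also alternatives. Under an any-endpoint rule power rises above 90%. Under an all-endpoints rule type I error is at or below 5%.

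**A reader might take the wording of the Abstract's objective as a joint success rule.** It lists two windows and names no time point, so it does not settle the question.

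**A reader might add biochemically confirmed abstinence to the primary family, or treat relapse as a rival primary.** Neither is supported. The confirmed versions are nowhere labelled primary, and the biochemical section describes cotinine as a check on self-report. The conflict over relapse is one of labelling: Table 1 marks tobacco use or abstinence as primary, and the heading is most likely loose wording for smoking status. It still needs correcting, because that section goes on to give relapse its own definition.

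**Conclusion.** The concern holds in this limited form. Four endpoints are called primary, none is chosen to decide success, and N=940 with 80% power matches one unnamed comparison at an inferred two-sided 5%.

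- **Any endpoint suffices:** false-positive rate about 12–13% (8–9% for two times on one window), with power above 90%.
- **All four required:** type I error at or below 5%, with power about 58–64% (68–72% for both times on the 30-day window).

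These ranges rest on an assumed 7-day rate of 30%, assumed correlations of 0.6 to 0.9 and a uniform 10-point effect. The reproduction of N rests only on the article's figures and the inferred alpha. The sample size is not wrong: it is adequate for one named endpoint with a 25% control rate. The point matters because it decides what counts as a positive trial.

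**What to change.** Before arm-level outcome data are examined:

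1. Name one window and one time point as the primary outcome, and use that wording in the Abstract, Textbox 1, Study Design and the Aim 1 analysis.
2. Make the other three endpoints secondary, or test them in a stated fixed order.
3. State the alpha and sidedness, and say that the 80% power and the 25% control rate refer to the named endpoint.
4. Reword the measures heading so that it agrees with Textbox 1, where relapses are secondary, and state that biochemically confirmed abstinence is supportive.

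The choice of window and time is the investigators' to make and justify.

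Alternatively, keep several primary endpoints, state a co-primary or alpha-allocation rule, and restate the power: about 60% if all four are required (under the assumptions above), 62% per test with Bonferroni over four, or 71% per test over two. Enrolment of 940 is complete, so N cannot readily be raised to the 1336 or 1138 that those splits would need for 80%.

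The first route costs only wording and leaves N unchanged. Its downside is that a significant result on a lower-ranked endpoint alone cannot be claimed as primary success. The Results section reports that 337 participants had finished 12-month follow-up by 31 August 2025, so the change should be dated and made promptly.
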